## Background

Chagas’ disease, or American trypanosomiasis, is caused by the protozoan parasite *Trypanosoma cruzi*. It is a major cause of morbidity and mortality in the Americas, and an estimated 9 million persons are currently infected [1]. Of particular concern is the fact that mothers with Chagas’ disease can transmit *T. cruzi* to their fetuses [2].

Mother-to-child transmission of *T. cruzi* has all the characteristics required to be a public health priority, as it is relatively frequent, severe, identifiable, and treatable [3]. In reality, it is a neglected disease and a missed opportunity. Therefore, it is urgent to better understand the epidemiology of mother-to-child transmission and to develop effective prevention programs.

*T. cruzi* has been divided into Discrete Typing Units (DTUs): *T. cruzi* I (TcI) and *T. cruzi* Non-TcI (II-VI). In humans, TcI is predominant in Mexico and Central America, while Non-TcI is predominant in most of South America, including Argentina [4]. In recent studies from Argentina, the risk of congenital transmission has been estimated to vary between 2.6% and 7.9% [5-8]. By contrast, we know very little about the congenital transmission of TcI. It has been suggested that congenital transmission of *T. cruzi* is strain related [2,9], and there is an urgent need to know if TcI transmits differently than Non-TcI. Our primary hypothesis is that congenital transmission rates are different for TcI versus Non-TcI.

*T. cruzi* infected women living in regions where TcI is predominant could differ in terms of risk factors for transmitting *T. cruzi* to their offspring. Low maternal age, low parity, HIV/AIDS, exposure to vectors and high parasitic load have been reported as risk factors for congenital *T. cruzi* infection [9-14]. Family clustering has been observed in Argentina [15], suggesting that some mothers might be predisposed to transmit repeatedly.

There is limited information about the perinatal outcomes of infected infants in low endemicity areas. Congenital *T. cruzi* infection has been associated with premature rupture of the membranes and preterm births, in addition to neonatal complications [14]. Further studies are needed to document the impact of *T. cruzi* infection on perinatal outcomes.

The specific aims of this study are:

– 1. To determine the rate of congenital transmission of TcI compared to Non-TcI;

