### Variables

The exposure to TcI will be defined by *T. cruzi* genotyping showing TcI on maternal blood and/or cord blood. In the absence of successful *T. cruzi* genotyping on maternal or cord blood, births occurring in Mexico or Honduras will be considered exposed to TcI.

The exposure to Non-TcI will be defined by *T. cruzi* genotyping showing Non-TcI on maternal blood and/or cord blood. In the absence of successful *T. cruzi* genotyping on maternal or cord blood, births occurring in Argentina will be considered exposed to Non-TcI.

The exposure to both TcI and Non-TcI (co-infection) will be defined by *T. cruzi* genotyping of both TcI and Non-TcI on maternal blood and/or on cord blood, or of TcI on maternal blood and Non-TcI on cord blood, or of Non-TcI on maternal blood and TcI on cord blood.

The primary outcome (Specific Aim 1) will be the congenital *T. cruzi* infection, which will be defined as the presence of one or more of the following criteria:

– Presence of parasites in cord blood (direct parasitological microscopic examination); and/or

– Presence of parasites in infant’s blood at 4–8 weeks (direct parasitological microscopic examination); and/or

– Persistence of *T. cruzi*-specific antibodies at 10 months, as measured by two tests.

A seropositive mother will have at least one positive rapid test on cord blood and a positive ELISA on maternal blood.

The mothers’ characteristics and exposure to vectors variables (Specific Aim 2) that will be collected include:

– Maternal age;

– Parity (including current birth);

– Infected sibling (yes/no) (siblings previously treated for *T. cruzi* infection will be presumed as having been infected);

– Maternal parasitic DNA amount;

– HIV serology (according to tests performed routinely in each country);

– Presence of vectors in the household (Infestation) (yes/no).

– Location in an area with risk of vectorial transmission (yes/no)

The birth outcomes (Specific Aim 3) to be measured are the following:

– Premature rupture of the membranes (PROM), defined as rupture of membranes before admission or before the onset of contractions, whatever the timing of the rupture; [14]

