### Blood samples and laboratory evaluations

Immediately after the clamping and sectioning of the umbilical cord, 20 ml of venous umbilical cord blood will be collected from the placental side of the cord with a needle and syringe and placed in EDTA (15 ml) and heparinized (5 ml) tubes following an established protocol. After obtaining informed consent, rapid serological tests will be performed on cord blood within the next six hours. If both rapid serological tests are negative, the mother will be excluded from the study and we will select a randomized sample of the umbilical cord blood samples to be stored.

If one of the cord blood rapid serological tests is positive, parasitological examinations will be performed immediately, and samples will be stored for further testing (10 ml on EDTA will be stored for molecular testing and 5 ml for further serological testing). 15 ml of venous maternal blood will be collected in EDTA tubes from mothers and also stored (10 ml for molecular testing and 5 ml for further serological testing).

The samples to be stored for further molecular testing will be immediately mixed with the same volume of guanidine-HCl 6M, EDTA 0.1 M (pH 8), and kept at 4°C until processed. This standard blood treatment contributes to the stabilization of the sample’s DNA content and improves its long-term conservation as well as favors the parasitic DNA dispersion into the entire sample. Blood samples for further serological tests will be stored in part on filter paper kept at 4°C until use, and additional plasma samples will be frozen at -20°C until use.

During the 4-to-8-week follow-up household visits, 2 ml of blood will be collected in heparinized tubes from the infant by venipuncture, or 6 heparinized capillary tubes will be collected by heel stick and transported to the laboratory in mobile refrigerators for parasitological examination within a maximum of six hours. In those cases in which it is not possible to collect enough blood to fill 6 capillary tubes, collecting a blood sample large enough to fill one capillary tube will be considered acceptable. Finger pricks will be used for siblings. A half drop of blood (10 μl) will be collected from the finger with a disposable pipette for the rapid serological test. An additional 100 μl (5 drops) of blood will be stored on filter paper for ELISA study.

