### Analysis plan

We will compute the rate of congenital transmission among seropositive mothers according to the exposure to TcI or Non-TcI with the corresponding confidence intervals and compare them using binomial exact tests. A seropositive mother will have at least one positive rapid test on cord blood and a positive ELISA on maternal blood. Cases with TcI/Non-TcI co-infection and with maternal HIV/AIDS will be analyzed separately, and transmission rates will be compared to the rest of the population.

In a second step, we will repeat the analysis after excluding infants with negative parasitological examinations and negative PCR on cord blood, and with a history of transfusion and/or organ transplant, and/or who are living in households exposed to the vector (presence of vectors and/or location in an area at risk of vector transmission). The resulting congenital transmission rate will be a more conservative estimate, which will be less likely to be biased by non-congenital routes of transmission. We will also stratify according to breastfeeding (yes/no), another potential route of neonatal transmission.

We will adjust the comparison of TcI/Non-TcI transmission rates for potential confounders:

– Maternal age at delivery (in five-year categories);

– Parity (primiparae/multiparae);

– Presence of vectors in the household (yes/no);

– Maternal parasitic DNA amount;

– Mode of delivery (C. section vs. vaginal); and

– Infected sibling (yes/no) (siblings previously treated for *T. cruzi* infection will be presumed as having been infected).

Mantel-Haenszel chi-square tests will be used for stratified analyses, which will take one categorical factor into account at a time. A logistic regression will be also performed and will include all potential confounders. Adjusted odds ratios (OR) and confidence intervals will be estimated.

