We will describe birth outcomes (PROM, gestational age, birthweight, head circumference, length, and neonatal complications) of infected and uninfected infants by calculating proportions and confidence intervals for categorical variables (including preterm birth and low birthweight) and means and standard deviations for continuous ones. In a next step, we will stratify the analysis by DTU (TcI/Non-TcI). We will compare intrauterine growth restriction (IUGR) rates. A newborn will be classified as IUGR if its birthweight is below the tenth percentile of the sex-specific birthweight for gestational age curves proposed by Williams et al. [42] for single and multiple births. These growth curves are recommended by the WHO as reference patterns for international comparisons [43,44]. We will use the same reference for the three countries to allow for comparison among sites. In addition, we will also compute IUGR rates according to a more recent U.S. reference curve [45] for single live births to facilitate comparisons with the U.S. literature. We will also analyze birthweight data of infected and uninfected siblings by calculating proportions of low birthweight and “very small babies” and confidence intervals, mean birthweights, and standard deviations.

We will use STATA Version 8.0 [46] software for data analysis.

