### Ethical aspects

The described protocol with informed consent and assent for children between 7 and 17 years old was approved by the Institutional Review Board of Tulane University and the ethics committees of the respective collaborating institutions in Argentina, Honduras, and Mexico.

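### Sibling serology cannot separate congenital from later infection, yet the sibling birthweight comparison and the infected-sibling variable lack the safeguard that the plan gives to the index infants' transmission rate

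*Protocol article*

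**What the plan says.** **How siblings are tested.** Under Blood samples and laboratory evaluations, "Finger pricks will be used for siblings", with a rapid test from one small drop, and "An additional 100 μl (5 drops) of blood will be stored on filter paper for ELISA study". Table 1 lists only Stat-Pak and ELISA for them. Follow-up places the test at the first home visit, or at 10 months if that visit missed the child. No cord blood, early parasitological or PCR result is planned for siblings.

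**At what age.** No upper limit is given. Ethical aspects mentions "assent for children between 7 and 17 years old". The enrolled women are adults and the index children are newborns, so this age group can only be siblings.

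**How infection is defined.** Variables lists infected sibling as a yes/no maternal characteristic for Aim 2, without a criterion for route. Siblings treated earlier "will be presumed as having been infected". Background gives a reason for interest in siblings: family clustering, "suggesting that some mothers might be predisposed to transmit repeatedly".

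**How it is used.** The Analysis plan describes sibling birthweight by infection status ("We will also analyze birthweight data of infected and uninfected siblings by calculating proportions of low birthweight", with very small babies, means and standard deviations). It also lists infected sibling among the confounders.

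**What is guarded.** For index infants the Analysis plan repeats the transmission analysis. It leaves out those with no parasitological or PCR evidence in cord blood who also had a transfusion, a transplant or household vector exposure. The resulting rate is one "which will be less likely to be biased by non-congenital routes of transmission". No such repeat is stated for siblings or for the Aim 3 infant tables.

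**The concern.** Antibodies in a child of several years show infection at some time since conception. They do not show whether it came from the mother, a vector or a transfusion. Birthweight is fixed at birth, so a contrast by infection status is informative only for infection acquired before birth. Each sibling infected later moves the infected group's birthweight towards that of the uninfected. A real effect of congenital infection would look smaller than it is, and could be missed.

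The Aim 2 variable has the same weakness. If infected sibling is meant to mark mothers who tend to transmit, infections from the local vector add children who say nothing about the mother. A difference between regions could then reflect vector transmission.

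The plan accepts this argument for index infants, who have had at most about 10 months of exposure when tested. It applies with more force to siblings, who may have had years.

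**Working it through.** **1. What the plan gives.** For siblings it states no number, no expected birthweight difference and no rate of infection after birth. Its one design figure is power above 80% for 1% versus 5% with 300 mothers per group. With a two-sided 5% level (assumed, as none is stated) this reproduces as 82.1% by the normal approximation and 79.8% by Fisher's exact test. It does not enter this point.

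**2. Which analyses have the safeguard.**

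| Analysis | Restricted repeat for non-congenital routes? |
|---|---|
| Index infants, transmission rate | Yes |
| Index infants, Aim 3 birth outcomes | Not stated |
| Sibling birthweight | Not stated |
| Infected sibling, Aim 2 and covariate | Not stated |

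**3. Congenital share of seropositive siblings.** Let c be the proportion infected congenitally and v the proportion of the rest infected after birth and before testing. With accurate serology the seropositive proportion is c + (1 − c)v, so

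share = c / [c + (1 − c)v].

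Inputs: c = 1% and 5% are the planning rates for TcI and Non-TcI under Sample size, borrowed here for siblings. The values of v are assumptions.

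| v (assumed) | c = 1% | c = 5% |
|---|---|---|
| 0.5% | 0.01 / 0.01495 = 67% | 0.05 / 0.05475 = 91% |
| 1% | 0.01 / 0.0199 = 50% | 0.05 / 0.0595 = 84% |
| 2% | 0.01 / 0.0298 = 34% | 0.05 / 0.069 = 72% |

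**4. Effect on the birthweight contrast.** Let D be the true mean difference caused by congenital infection. Suppose siblings infected later have the same mean birthweight as uninfected siblings. The contrast of seropositive with seronegative siblings is then share × D. At c = 1% it shows about two thirds to one third of D, and at c = 5% about nine tenths to seven tenths.

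**5. Is there a direction by strain?** Entomological data expects 100 households of seropositive mothers in Mexico, 300 in Honduras and 200 in Argentina.

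- Take v = 2% in Mexico and 0.5% elsewhere, with c = 1% for TcI and 5% for Non-TcI. The TcI seropositive proportion is [100 × 0.0298 + 300 × 0.01495] / 400 = 0.01866, a share of 54%. Non-TcI is 91%.
- Take v = 1% everywhere and c = 5% in both groups. The shares are 84% and 84%, so there is no gap.
- Take v = 0.5% in Mexico and Honduras and 3% in Argentina, with c = 1% and 5%. TcI is 67% and Non-TcI is 0.05 / (0.05 + 0.95 × 0.03) = 64%, so the order reverses.

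The direction follows from what is put in, not from the documents.

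**6. Aim 3 infants.** The primary outcome definition accepts antibodies persisting at 10 months as sufficient alone. An infant infected after birth can therefore enter the infected column of the birth outcome tables. The documents do not allow this to be sized; the window is at most about 10 months.

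**The case against.** **Nothing calls these siblings congenital cases.** That is correct. The variable is infected sibling, and the remark about repeat transmission is background. The point rests on the use made of the status: a birth outcome is contrasted by it, and only prenatal infection can bear on a birth outcome.

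**Vector exposure is partly handled.** Household infestation and risk area are reported for Aim 2 beside infected sibling, and the logistic model holds household vectors together with it. This eases the covariate problem. It leaves out risk area, sibling age and sibling transfusion history, and it does nothing for the birthweight description.

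**The analysis is descriptive and secondary.** This also stands. The sibling sentence promises proportions, means and intervals, with no test. A further sensitivity analysis might sit in a document not shown. But the article does write out the safeguard, and confines it to one analysis.

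**A stronger reading.** A reader might infer that the distortion is worst where TcI predominates and would create a false strain difference. The documents do not support this. Entomological data expects limited infestation in Honduras as well as Argentina, and only Mexico to differ. Honduras supplies 300 of the 400 expected households in the two TcI countries. Those expectations describe present infestation, not siblings' past exposure. The Analysis plan does not stratify siblings by strain. With equal v, any gap in the shares comes solely from entering 1% against 5%.

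**Conclusion.** The concern holds in a limited form. The sibling birthweight contrast, the infected-sibling variable and the Aim 3 infant tables use an infection status that can include infections acquired after birth. The plan's own guard against such infections does not reach them. The birthweight contrast is diluted towards no difference, and the sibling variable partly measures local vector transmission.

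The size cannot be fixed from the documents. The shares of 67% to 34% (c = 1%) and 91% to 72% (c = 5%) rest on the assumed v of 0.5% to 2%, on planning rates borrowed from index infants and on accurate serology. Proportional dilution also assumes that later-infected and uninfected siblings have the same mean birthweight. If vector-exposed households differ in birthweight for other reasons, confounding is added and may act either way.

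Higher exposure is suggested for Mexico only, and no direction by strain follows. The primary unadjusted comparison of transmission rates and its power are not affected.

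**What to change.** 1. Call the variable 'seropositive sibling' throughout, so that no route is implied.
2. Repeat the sibling birthweight comparison and the infected-sibling variable with the Analysis plan's exposure restriction applied symmetrically. Take both seropositive and seronegative siblings only from households without infestation and outside at-risk areas, and only if they have no transfusion or transplant history. Show this beside the unrestricted result.
3. In the Aim 3 infant tables, show separately the infants positive only by 10-month serology who had a postnatal exposure.

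The restriction must apply to both groups. Dropping only exposed seropositive siblings and keeping every seronegative one would confound infection with household setting. It would also artificially lower infected-sibling prevalence in the more exposed regions.

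The change is to analysis wording. Household infestation, area risk and sibling transfusion and transplant history are already to be collected. The price is fewer infected siblings and wider intervals. A limit remains: exposure is taken from collections during the study, village records of the past five years, or published risk maps for Yucatan, and may not match older siblings' past exposure. The restricted result is therefore less contaminated, not clean.

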### Ethical aspects

The described protocol with informed consent and assent for children between 7 and 17 years old was approved by the Institutional Review Board of Tulane University and the ethics committees of the respective collaborating institutions in Argentina, Honduras, and Mexico.

## Abbreviations

CDC: Centers for Disease Control and Prevention; CRF: Case Report Form; DHS: Demographic and Health Survey; DTU: Discrete Typing Units; EDTA: Ethylenediaminetetraacetic Acid; ELISA: Enzyme-linked Immunosorbent Assay; GIS: Geographic Information Systems; GPS: Global Positioning System; IUGR: Intrauterine Growth Restriction; NIAID: National Institute of Allergy and Infectious Diseases; NIH: National Institutes of Health; PAHO: Pan American Health Organization; PCR: Polymerase Chain Reaction; PROM: Premature Rupture of Membrane; qPCR: Quantitative real-time Polymerase Chain Reaction; TcI: *Trypanosoma cruzi* DTU I; WHO: World Health Organization.
